### Study procedure

Physiotherapy practices that are willing to participate in the study will be screened on eligibility by a researcher (TK or RA). Cluster randomization will be performed at the level of the participating physiotherapy practices. Each practice will be randomly assigned to the intervention (e-Exercise LBP) or the usual care group by an independent researcher using an a priori created computer-generated random sequence table. Physiotherapists in the intervention group will receive two 4-h training sessions about e-Exercise LBP and the study procedures. In the usual care group, physiotherapists will receive one 4-h training session in current best evidence practice according to the guideline LBP of the Royal Dutch Association for Physiotherapy (KNGF) [10] and the study procedures.

Physiotherapists, or their colleagues who will handle the initial registration of the patient, will orally inform potentially eligible patients about the study. Interested patients will receive the patient information letter by e-mail and will be contacted by one of the researchers (TK or RA) by phone prior to the first physiotherapy appointment. When a patient is willing to participate, a face-to-face appointment with one of the researchers (TK or RA) will be scheduled to screen in- and exclusion criteria and to provide written informed consent. After signing informed consent, the patient’s physiotherapist will be informed about the patient’s participation.

During the study period, both patient groups can still receive care from any other healthcare professional.

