#### Effectiveness

The primary purpose of this study is to estimate the effectiveness of e-Exercise LBP for improving physical functioning compared to usual primary care physiotherapy in patients with LBP. The primary analysis time point for the study will be 12 months following baseline, however 3- and 24-month changes will also be evaluated. To evaluate the overall effectiveness of e-Exercise LBP, differences in change scores per group and time period will be estimated on primary and secondary outcomes using linear mixed models (LMM) with random effects to control for correlation within patients and physiotherapists [70, 71]. The three-level hierarchy will exist of repeated measurements (level 1), nested within patients (level 2), nested within physiotherapists (level 3). Analysis will be controlled for baseline variables that have been shown to be related to physical functioning, e.g. age, gender, pain severity scores, duration of pain [72–74].

In addition, a per-protocol analysis that only includes patients of the intervention group which were adherent to the smartphone application and the entire usual care group will be performed. Patients will be considered to be adherent to the smartphone application if they used the application for at least 2/3rd of the duration (i.e. 2 out of 3 week for the “low-risk” profile and 8 out of 12 weeks for the “medium- and high-risk” profile) [35, 75]. Per-protocol analyses will be performed using LMM with the same 3-level structure, and will be controlled for the same variables as the primary analysis.

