Besides further development of the e-Exercise LBP intervention, several important methodological considerations were made with respect to the study design of the e-Exercise LBP trial. A first consideration was the use of a cluster-randomized controlled design to avoid contamination between the e-Exercise LBP intervention and usual physiotherapy care at the level of the participating physiotherapist. Cluster-randomization at the level of the participating physiotherapy practices ensures that each participating physiotherapist working in the same physiotherapy practice, delivers the same intervention [89]. The influence of clustering will be corrected using LMM in the statistical analysis.

Since the e-Exercise LBP intervention aims to improve physical functioning, this outcome measurement was selected as primary outcome measurement. Intervention duration will last up to 3 months, but a 12-month evaluation will provide insight in the effectiveness of e-Exercise LBP on the long-term. However, with respect to the cost-effectiveness, it is hypothesized that patients who followed e-Exercise LBP are able to manage recurrent complaints independently, resulting in reduced health-care usage or sickness absence. Since a 12-month follow-up might be too short to study this hypothesis, we added a 24-month follow-up focusing on the management of recurrent complaints.

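### On the natural reading of the primary model, the cluster effect cancels from the 12-month change contrast, so clustering may go uncorrected

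*Protocol article*

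**What the plan says.** In the protocol article, the Effectiveness part of the statistical analysis defines the treatment effect as follows: "differences in change scores per group and time period will be estimated on primary and secondary outcomes using linear mixed models (LMM". The model is fitted "with random effects to control for correlation within patients and physiotherapists", and its levels are "repeated measurements (level 1), nested within patients (level 2), nested within physiotherapists (level 3". On timing: "The primary analysis time point for the study will be 12 months following baseline". On covariates: "Analysis will be controlled for baseline variables that have been shown to be related to physical functioning"; the examples given are age, gender, pain severity and pain duration. Baseline ODI is neither named nor excluded. The per-protocol analysis reuses the same three-level structure and covariates.

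On clustering, the Study procedure section states: "Cluster randomization will be performed at the level of the participating physiotherapy practices". The Sample size calculation allows for clustering with an ICC of 0.05 and an average cluster size of 5. The Discussion concludes: "The influence of clustering will be corrected using LMM in the statistical analysis".

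Two further places bear on what counts as a repeated measurement. The Measurements section lists baseline as the first of four data-collection points for the primary outcome. The Sample size calculation, when it speaks of repeated ODI measures, gives a correlation between baseline and follow-up.

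**The concern.** Read together, these passages point to one model. The level-1 outcomes are ODI scores at baseline, 3, 12 and 24 months, the arm effect is a group-by-time term, and each patient and each physiotherapist has a random effect. No random slope or cluster-by-time effect is mentioned.

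If the physiotherapist effect is a single intercept, it is the same at baseline and at 12 months and drops out of the change between them. The standard error of the 12-month contrast then does not depend on the estimated cluster variance. If some therapists or practices get better results than others, that variation arises during treatment and lies in the change. The model would treat it as independent patient noise. A practice intercept would cancel in the same way, so the problem is separate from the question of which unit belongs at level 3.

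At stake is the size of the primary test. The trial recruits for a design effect of 1.20 that the test would then leave out, and confidence intervals would be somewhat too narrow.

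**Working it through.** **Inputs.** From the Sample size calculation: ICC 0.05, cluster size 5, SD 14.5, difference 6, baseline to follow-up correlation r = 0.5, power 80%, α = 0.05. From the Statistical analysis section: two-sided testing. Assumed, because the article does not give it: c, the correlation between a cluster's baseline effect and its 12-month effect.

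**1. The plan's own figure.**
- Per arm: 2 × (14.5 × (1.960 + 0.842)/6)² = 91.68, so 183.36 in total.
- Design effect: 1 + (5 − 1) × 0.05 = 1.20, giving 220.03.
- Times 0.75: 165.02, matching the stated 165. Then 165/0.80 = 206.25, rounded up to 207.

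The plan does budget for clustering: without the design effect, 183.36 × 0.75 = 137.52.

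**2. The cancellation.** Write the score as y = (arm-by-time mean) + u(cluster) + p(patient) + e. The change from baseline to 12 months is (difference in means) + e(12) − e(0); both u and p are gone. With n patients in two equal arms, the model's variance for the contrast is 2σₑ² × 4/n. In SD units with r = 0.5, 2σₑ² = 2(1 − 0.5) = 1. For 34 clusters of 5 (n = 170) the model SE is √(4/170) = 0.153, whatever the cluster variance.

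Fitted three-level models agree. With 2 × 20 clusters of 5 patients and 4 visits, adding a constant cluster effect with an SD of 10 ODI points left the SE of the arm-by-month-12 term unchanged in two data sets (2.0834 both times; 1.9677 both times). The estimated cluster variance rose from 11 to 69 and from 0 to 112.

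**3. What the SE should be.** If cluster effects vary over time, the between-cluster variance of change is 2 × 0.05 × (1 − c) × SD², and the total variance of change is 2(1 − 0.5)SD² = SD². So the ICC of change is 0.10(1 − c), the design effect is DE = 1 + 4 × 0.10(1 − c), and the true size of the nominal 5% test is 2(1 − Φ(1.96/√DE)).

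| c (assumed) | ICC of change | DE | SE too small by | True size |
|---|---|---|---|---|
| 1 | 0 | 1.00 | 0% | 5.0% |
| 0.8 | 0.02 | 1.08 | 3.8% | 5.9% |
| 0.5 | 0.05 | 1.20 | 8.7% | 7.4% |
| 0 | 0.10 | 1.40 | 15.5% | 9.8% |

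If a cluster variance of 0.05 arises only after baseline, the ICC of change is 0.05, as in the c = 0.5 row. The true SE is then 0.153 × √1.20 = 0.168, or about 2.4 ODI points against 2.2 from the model (times 14.5).

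**4. Simulation under no effect** (34 clusters of 5, 4 time points, 20,000 runs, z test), rejection rate at 12 months:

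| Cluster effects | Raw scores with baseline, constant intercepts | 12-month change as outcome, cluster intercept | Baseline-adjusted 12-month score, cluster intercept |
|---|---|---|---|
| Constant over time | 4.9% | 4.3% | 4.9% |
| c = 0.8 | 6.0% | 4.9% | 4.9% |
| c = 0.5 | 7.8% | 5.4% | 5.2% |
| Only after baseline | 7.6% | 5.6% | 5.4% |

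In the last row the first model reported a mean SE of 0.153, the same as a model with no cluster term, against an empirical SE of 0.168. Using a t reference with 32 degrees of freedom in that model still gave 6.5%, so degrees of freedom alone do not repair it. A separate run with 40 clusters of 5 gave 7.5% at c = 0.5 and 9.5% at c = 0.

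The last two columns use the 12-month value alone, and the baseline adjustment uses a fixed slope of 0.5.

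**The case against.** The strongest reply is that the article does not commit to the model in which the cancellation occurs. It says random effects, not intercepts that are constant over time. Changes at 3, 12 and 24 months are also repeated measurements within patients within physiotherapists, so the hierarchy fits change scores as the dependent variable too. It equally allows baseline ODI as a covariate. Under either form the same cluster intercept does its work. The sample size is no evidence for the harmful model: its factor of 0.75 equals 1 − r², the baseline-covariate form, whereas a pure change contrast has 2(1 − r) = 1.0 and would need 220. Covariance structure is also something an article commonly leaves to the full analysis plan.

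Much of this stands. A reader might infer that the plan certainly leaves clustering uncorrected, that the primary p-value is certainly too small, or that the Discussion's statement is simply false. The article supports none of these. The model form is not pinned down, and cancellation alone does no harm: if cluster effects are constant they cancel from the data as well as from the model, and the test holds its level. Nor does the problem reach every outcome. Recurrent episodes are counted over follow-up with no baseline value to subtract.

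Two parts do not stand. The factor 0.75 also equals (1 + r)/2, so it does not establish the covariate form. And this is not merely absent detail: the article itself fixes the estimand and the hierarchy, counts baseline among the repeated measures, omits baseline ODI from its example covariates, and asserts that the correction is made. The most natural model built from those statements does not deliver it.

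**Conclusion.** The point holds conditionally. On the natural reading, the primary 12-month contrast gets essentially no correction for clustering. If cluster effects also differ between baseline and 12 months, the nominal 5% test has a true size of about 6% (c = 0.8) to 7.4% (c = 0.5, or variance arising only after baseline), and up to about 9.8% at c = 0. These figures rest on the protocol's ICC of 0.05, cluster size of 5 and correlation of 0.5, and on assumed values of c.

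Changing cluster effects are plausible here. Under Study procedure, a researcher contacts the patient before the first physiotherapy appointment, and the physiotherapist learns of participation only after consent. Usual-care content and number of sessions are left to the therapist, and intervention therapists may deviate from the programme. Therapist influence on ODI should therefore build up mainly after baseline.

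The inflation is moderate, and it is absent if cluster effects are constant over time, if change scores are the dependent variable, or if baseline ODI is a covariate. It affects the primary outcome, secondary outcomes with a baseline value, and the per-protocol analysis that reuses the structure.

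**What to change.** In the Effectiveness section, state a cluster effect that acts on the 12-month contrast, in one of two ways:

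- model only the post-baseline scores as outcomes, with baseline ODI as a covariate and a cluster random intercept; or
- keep baseline as an outcome and add a cluster-by-time random effect, so that a cluster's follow-up effect can differ from its baseline effect.

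In either case, test the arm effect with between-cluster degrees of freedom, and use the same form for the per-protocol analysis and for secondary outcomes with a baseline value. If 3, 12 and 24 months are modelled jointly, a single intercept in the first option assumes the same cluster effect at all three visits; the second option does not need that assumption.

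The cost is a sentence or two of model specification and slightly wider confidence intervals. The second option also has one more variance component to estimate.

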### Participants

#### Primary care physiotherapy practices

Primary care physiotherapy practices will be invited by letter to participate in the study. Contact details of potential participating practices will be obtained from the professional network of the authors and a previous e-Exercise study [35]. Additionally, a recruitment advertisement will be placed in the online newsletter of The Royal Dutch Association for Physiotherapy (KNGF). Primary care physiotherapy practices are eligible to participate if at least five patients with non-specific LBP consult the practice for physiotherapy treatment each month. Each participating physiotherapy practice will be asked to enrol at least two physiotherapists in order to ensure continuity of care. All primary care physiotherapists, regardless of professional experience and education or specialization (e.g. manual therapist) are eligible to participate.

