##### Statistical analyses

Missing cost and effect data will be imputed using ‘Multivariate Imputation by Chained Equations’ and the results will be pooled using Rubin’s rules [87]. Cost differences (∆C) and effect differences (∆E) will be estimated using LMM, and will be corrected for the same baseline variables as the effectiveness analysis. To account for the highly skewed nature of cost data, bias-corrected and accelerated bootstrapping with 5000 replications will be used to estimate 95% confidence intervals around the cost differences (∆C). Incremental cost-effectiveness ratios (ICERs) will be calculated by dividing the difference in costs by the difference in effects (∆C/∆E). Uncertainty surrounding the ICERs will be graphically illustrated by plotting bootstrapped cost-effect pairs on cost-effectiveness planes and by estimating cost-effectiveness acceptability curves. To test the robustness of the study results, several sensitivity analyses will be performed [88].

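### Practices are randomised, but the mixed model stops at the physiotherapist, so clustering at the randomised level is only partly modelled

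*Protocol article*

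**What the plan says.** Under Study procedure the unit of allocation is explicit: "Cluster randomization will be performed at the level of the participating physiotherapy practices". Under Primary care physiotherapy practices, the practice is a level above the individual therapist: "Each participating physiotherapy practice will be asked to enrol at least two physiotherapists in order to ensure continuity of care".

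The Effectiveness section, under Statistical analysis, specifies linear mixed models for the primary and secondary outcomes with "random effects to control for correlation within patients and physiotherapists". It then counts the levels: repeated measurements at level 1, "nested within patients (level 2), nested within physiotherapists (level 3"). The per-protocol analysis follows suit: "Per-protocol analyses will be performed using LMM with the same 3-level structure". No section adds a practice term.

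The Discussion explains randomisation by practice as a guard against contamination and then states: "The influence of clustering will be corrected using LMM in the statistical analysis".

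The Sample size calculation uses an intracluster correlation of 0.05 and an average cluster size of 5. It does not say whether either refers to the practice or to the physiotherapist.

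**The concern.** Treatment varies only between practices, so the treatment contrast has to be judged against variation between practices. Two physiotherapists in one practice always share the arm and the practice, yet the specified model treats them as independent units. It therefore counts more independent units per arm than were randomised.

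This is not a detail left to a fuller plan. The article names the levels, numbers them and ends the list below the randomised unit. The Discussion's assurance that clustering is corrected is then only partly met.

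At stake are the standard error, confidence interval and p-value for physical functioning at 12 months, and the same quantities for every secondary outcome and for the per-protocol analysis, which use the same structure.

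**Working it through.** **Inputs from the Sample size calculation:** difference 6 ODI points, SD 14.5, baseline to follow-up correlation 0.5, intracluster correlation 0.05, average cluster size 5, power 80%, α 0.05, dropout 20%. The significance level is two-tailed (Statistical analysis).

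**Step 1: reproduce the plan's own figure.**
- Per arm, unadjusted: 2 × [14.5 × (1.960 + 0.842) / 6]² = 91.68.
- Baseline adjustment: 1 − 0.5² = 0.75.
- Design effect: 1 + (5 − 1) × 0.05 = 1.20.
- Total: 2 × 91.68 × 0.75 × 1.20 = 165.02, against 165 stated.
- Dropout: 165 / 0.80 = 206.25, rounded up to 207, as stated.

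The sample-size arithmetic is sound, and it rests on a design effect of 1.20 at an unnamed level.

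**Step 2: what the model captures and what it leaves out.** Let m be patients per physiotherapist, k physiotherapists per practice, ρp the practice-level share of the correlation and ρt the additional physiotherapist share. A patient has m − 1 others under the same physiotherapist (correlation ρp + ρt) and m(k − 1) others in the same practice under a different physiotherapist (correlation ρp).

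- Design effect implied by the specified model: 1 + (m − 1)(ρp + ρt).
- True design effect: the same plus m(k − 1)ρp.
- SE factor (true SE / model SE): √(true / model).
- True two-sided type I error: 2 × [1 − Φ(1.96 / SE factor)].

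**Step 3: put in the numbers.** The total correlation is held at 0.05. Its split and the value of k are assumptions, because the article gives neither.

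| Reading of the 5 | m | k | ρp / ρt | Model | True | SE factor | Type I error |
|---|---|---|---|---|---|---|---|
| Per practice | 2.5 | 2 | 0 / 0.05 | 1.075 | 1.075 | 1.00 | 5.0% |
| Per practice | 2.5 | 2 | 0.01 / 0.04 | 1.075 | 1.100 | 1.012 | 5.3% |
| Per practice | 2.5 | 2 | 0.025 / 0.025 | 1.075 | 1.137 | 1.029 | 5.7% |
| Per practice | 2.5 | 2 | 0.05 / 0 | 1.075 | 1.200 | 1.057 | 6.4% |
| Per physiotherapist | 5 | 2 | 0.01 / 0.04 | 1.200 | 1.250 | 1.021 | 5.5% |
| Per physiotherapist | 5 | 2 | 0.025 / 0.025 | 1.200 | 1.325 | 1.051 | 6.2% |
| Per physiotherapist | 5 | 2 | 0.05 / 0 | 1.200 | 1.450 | 1.099 | 7.5% |
| Per physiotherapist | 5 | 3 | 0.01 / 0.04 | 1.200 | 1.300 | 1.041 | 6.0% |
| Per physiotherapist | 5 | 3 | 0.025 / 0.025 | 1.200 | 1.450 | 1.099 | 7.5% |
| Per physiotherapist | 5 | 3 | 0.05 / 0 | 1.200 | 1.700 | 1.190 | 10.0% |

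With k = 1 the extra term vanishes and the error is 5.0% whatever the split.

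**Step 4: check by simulation.** Balanced data were simulated under the null, with one outcome time point and 20,000 trials per scenario. For m = 5, k = 2 (8 practices per arm), the physiotherapist-only analysis rejected in 7.1% of trials with all 0.05 at practice level and in 6.0% with an even split. For m = 5, k = 3 (6 practices per arm) the figures were 9.8% and 7.4%. Analysis by practice rejected in 4.8% to 5.3% across all simulated scenarios.

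**The case against.** The strongest reply is that clustering is not ignored. The physiotherapist effect absorbs the practice variance shared by patients of the same physiotherapist, and the table credits the model with it. This stands: the correction is partial, not absent.

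It is also fair that the harm is conditional. The article does not place the 0.05 at either level. Practices are asked for at least two physiotherapists, which does not say how many will contribute patients. If practice variance is nil, or one physiotherapist per practice treats all its trial patients, nothing is lost. This limits the size of the point but does not justify a model that assumes a zero effect for the randomised unit.

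Three stronger readings are tempting, and the article does not support them.
- **Patients shared between physiotherapists.** A reader might infer from the wish for continuity of care that patients will see several physiotherapists, so that nesting within physiotherapist fails. No section says so, and Study procedure speaks of the patient's physiotherapist in the singular.
- **The economic evaluation.** A reader might infer that the cost and QALY analyses share the fault. Their Statistical analyses section names linear mixed models and says that "bias-corrected and accelerated bootstrapping with 5000 replications will be used to estimate 95% confidence intervals around the cost differences", but states neither the random-effect levels nor the resampling unit. No error is shown there.
- **The sample size.** A reader might conclude that it is too small, or that it certainly provided for clustering by practice. Neither follows, because the level of the 5 and of the 0.05 is not stated.

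**Conclusion.** The point holds as a mismatch between the randomised unit and the stated model. The primary, secondary and per-protocol models leave out correlation between patients of different physiotherapists in the same practice, so the Discussion's statement that clustering is corrected is only partly true.

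The direction is certain whenever practice variance is positive and more than one physiotherapist per practice contributes patients. The size is not known from this document:
- If the 5 is per practice, with two physiotherapists, the type I error is 5.0% to 6.4%, and the true standard error is at most about 6% larger than the one reported.
- If the 5 is per physiotherapist, the type I error is up to about 7.5% with two physiotherapists per practice and about 10% with three.

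These figures assume a total correlation of 0.05 for the analysed outcome, equal cluster sizes and one time point. The upper ends put all of the correlation at practice level. A flat statement that the error rate exceeds 5% would go beyond the document. The change is still worth making, because it concerns the primary analysis and costs little.

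**What to change.** In the Effectiveness section, add a random intercept for practice, giving measurements within patients within physiotherapists within practices, and use this structure for the primary, secondary and per-protocol models. State in advance that if one level cannot be estimated, the physiotherapist is dropped and the practice kept.

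In the Sample size calculation, say whether the 0.05 and the 5 refer to the practice or to the physiotherapist. If the economic mixed models and bootstrap are meant to follow the same structure, say so and have them respect practice too.

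The cost is a line of model specification and, where practice variance is present, slightly wider confidence intervals. No new data are needed, because the practice is the randomised unit and so is known for every patient.

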## Background

Low back pain (LBP) is the most common cause of disability in western society [1]. LBP causes a significant economic burden and is responsible for high direct healthcare costs as well as high indirect costs due to time lost from work [2]. LBP can be caused by a specific pathology or trauma; however, in more than 90% of cases an underlying disease is absent [3, 4]. The clinical course of this so-called ‘non-specific LBP’ varies; some people recover within a couple of days or weeks, and other people experience persistent disabling symptoms leading to chronic LBP [2, 5, 6]. Both national and international clinical LBP guidelines endorse patient education, advice on returning to normal activities and the prescription of home-exercises and/or supervised exercise therapy [7–10].

However, the effectiveness of physiotherapy in patients with LBP does not solely depend on providing the most adequate physiotherapy interventions. It also highly depends on patients’ adherence to prescribed (home-)exercises and recommended physical activity behaviour [11, 12]. Earlier research showed that 45–70% of patients do not adhere to prescribed exercises and physical activity recommendations [13–15], whereas adherent patients with LBP who continue a physically active lifestyle have a reduced risk of recurrent LBP [16]. Therefore, supporting self-management and adherence in patients with LBP is expected to be essential for the effectiveness of physiotherapy interventions on patients’ physical functioning and prevention of recurrent events.

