### Secondary outcome measures

*Pain intensity* is measured with an 11-point Numeric Rating Scale (NRS) for the average LBP intensity in the last week [44, 45, 47].

*Physical activity* is objectively measured using a 3-axial accelerometer, the Activ8 (ACTIV8, Valkenswaard, The Netherlands) [48]. The Activ8 is a valid instrument to detect sedentary behaviour (combination of lying and sitting), standing, walking, running, and cycling. Additionally, MET-values are given. The Activ8 measures with 12.5 Hz, an epoch of 1 s a sample interval of 5 s. Every 5 min a summary is stored of the different postures and MET-values [49]. In addition, participants are requested to fill out a short activity diary about unusual activities and reasons for device removal.

*Patient self-reported adherence to prescribed home exercises* is measured by the Exercise Adherence Rating Scale (EARS). Besides that, the EARS measures the exercise prescription and the reasons for (non-) adherence [50].

*Physiotherapist based assessment of adherence to prescribed home exercises* is measured by the Exercise Adherence Scale (EXAS). The EXAS is an interview-based questionnaire which is used by the physiotherapist during face-to-face care to determine both the qualitative performance of the recommended home exercises and the agreement between recommended home exercises and patient reported adherence [51].

*Adherence to the smartphone application* is measured in the experimental group only by means of quantitative data about usage (e.g. completed modules). The data is automatically stored on the backend of the smartphone application.

*Fear avoidance beliefs about physical activity and work is* measured using the Fear-Avoidance Beliefs Questionnaire (FABQ). The FABQ assesses the fear of movement/(re)injury and consists of items related to physical activity and work [52].

*Pain catastrophizing* is measured by the Pain Catastrophizing Scale (PCS) The PCS is a self-report measurement tool that provided a valid index of catastrophizing in clinical and non-clinical populations [53, 54].

*Self-efficacy*, i.e. the patients beliefs in their efficacy to influence events that affect their lives [55], is measured using the General Self-efficacy Scale (GSE Scale) [56–58].

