### Statistical analysis

Descriptive statistics (e.g. means and proportions) will be used to explore baseline comparability. To investigate selective attrition, general characteristics and primary baseline variables of dropouts and non-dropouts will be compared All analyses will be performed according to the ‘intention-to-treat’ principle. Missing data for all outcomes and cost measures will be imputed using ‘Multivariate Imputation by Chained Equations’ under the assumption that data are missing at random given baseline confounders. For all analysis, a two-tailed significance level of *p* < 0.05 is considered to be statistically significant. All analyses will be carried out using IBM SPSS Statistics version 24.0 (Amork, New York, USA).

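### The supplementary per-protocol analysis selects on app adherence in one arm only, so its contrast is confounded by any prognostic difference that adjustment leaves between adherers and non-adherers

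*Protocol article*

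**What the plan says.** All references are to the protocol article.

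- **Main principle** (Statistical analysis): "All analyses will be performed according to the ‘intention-to-treat’ principle". The same section applies a two-tailed 5% significance level to every analysis.
- **Additional analysis** (Effectiveness): the article adds "a per-protocol analysis that only includes patients of the intervention group which were adherent to the smartphone application and the entire usual care group".
- **Adherence rule** (Effectiveness): "Patients will be considered to be adherent to the smartphone application if they used the application for at least 2/3rd of the duration". This means 2 of 3 weeks for the low-risk profile and 8 of 12 weeks for the medium- and high-risk profiles.
- **Where adherence is observed** (Secondary outcome measures): app adherence "is measured in the experimental group only by means of quantitative data about usage".
- **Adjustment** (Effectiveness): the per-protocol model keeps the three-level structure and "will be controlled for the same variables as the primary analysis". Those variables are baseline factors related to physical functioning, "e.g. age, gender, pain severity scores, duration of pain".

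The article gives no weighting for adherence and no caution on how the per-protocol result should be interpreted.

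**The concern.** Randomisation of practices makes the whole intervention arm comparable with the whole usual care arm. It does not make app users in one arm comparable with everybody in the other. The usual care arm contains patients who would have fallen short of the threshold had they been given the app. They cannot be identified, so they stay in, while their counterparts in the intervention arm are dropped.

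Three features of the plan make a prognostic difference plausible:

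- The Background itself ties adherence to outcome: it reports less recurrence among adherent patients who remain physically active.
- The threshold differs by risk profile. If 2 of 3 weeks is easier to reach than 8 of 12, the adherent set is enriched for patients at low risk of persistent pain, while usual care keeps the full risk mix. Risk group is not among the covariates given as examples.
- The covariates are chosen because they relate to physical functioning, not because they predict app use. No baseline covariate fully captures stopping the app during treatment because of poor progress or early recovery.

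At stake is a secondary result, tested at 5%, that a reader could take for the effect of the intervention when the app is actually used.

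**Working it through.** **Step 1. The plan's own figure.** Inputs from Sample size calculation: difference 6, SD 14.5, power 80%, two-sided α 0.05, intracluster correlation 0.05, average cluster size 5, baseline to follow-up correlation 0.5.

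- Per arm, unadjusted: 2 × (14.5 × (1.960 + 0.842) / 6)² = 91.68
- Design effect: 1 + (5 − 1) × 0.05 = 1.2
- Baseline-adjustment factor: 1 − 0.5² = 0.75
- Total: 2 × 91.68 × 1.2 × 0.75 = 165.0
- With 20% dropout: 165 / 0.8 = 206.25, rounded up to 207

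Both stated totals reproduce, so the sample size is not at issue, and the same variance inputs can be used below.

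**Step 2. The per-protocol contrast when there is no effect.** Let p be the share that would adhere, A their adjusted mean outcome and N that of the others. By randomisation, usual care has the same mix:

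- Intervention adherers: A
- Entire usual care group: pA + (1 − p)N
- Difference: A − pA − (1 − p)N = (1 − p)(A − N)

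The bias is therefore (1 − p) × d, where d is the residual prognostic gap after adjustment.

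**Step 3. Assumed inputs.** The documents give neither p nor d.

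- The nearest figure for p is in the Background, which reports that "45–70% of patients do not adhere to prescribed exercises and physical activity recommendations". That implies 30 to 55% adherent, but it concerns exercise and activity advice, not weeks of app use. A value of 80% is therefore shown as well.
- d is taken as 4 or 6 ODI points, for illustration only.

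**Step 4. Standard error.** Residual SD = 14.5 × √0.75 = 12.56. With 165 / 2 = 82.5 usual care patients and 82.5p adherers, and the design effect of 1.2 kept in both arms for simplicity:

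SE = √(1.2 × 12.56² × (1/82.5 + 1/(82.5p)))

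This gives 3.15 at p = 0.30, 2.54 at p = 0.55 and 2.27 at p = 0.80. The false-positive rate is the chance that a normal estimate centred on the bias, with this SE, passes the two-sided 5% limit.

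| p | d | Bias (1 − p)d | Share of 6 points | False-positive rate |
|---|---|---|---|---|
| 0.30 | 4 | 2.8 | 47% | 14% |
| 0.30 | 6 | 4.2 | 70% | 27% |
| 0.55 | 4 | 1.8 | 30% | 11% |
| 0.55 | 6 | 2.7 | 45% | 19% |
| 0.80 | 4 | 0.8 | 13% | 6% |
| 0.80 | 6 | 1.2 | 20% | 8% |

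If d had the opposite sign, the bias would have the same size against e-Exercise.

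**The case against.** Much of the case on the other side stands.

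- **The analysis is supplementary.** The intention-to-treat mixed model at 12 months is the primary analysis and the sample size serves it. No decision rule depends on the per-protocol result. A reader might infer that the trial's main conclusion is compromised; nothing in the article supports that. Nor does the article say that it will present the per-protocol result as the effect of using the app.
- **The covariate list is open.** It consists of examples, and repeated ODI scores are modelled, so adjustment will remove part of the gap. How much is unknown, and unmeasured motivation may remain.
- **The size is assumed.** A reader might take 30 to 55% as the trial's expected app adherence. The article does not say so, and reminders and physiotherapist monitoring could push app use higher, where the bias is small.
- **The direction is not settled.** It is tempting to say that the analysis flatters e-Exercise. That is the likelier direction, but patients who recover early may also stop the app, and removing them would work the other way.
- **A complier-average causal effect is not a clear improvement.** It requires that assignment acts only through app adherence. Intervention practices also deliver stratified face-to-face care, and their physiotherapists receive two 4-hour training sessions rather than one. Suppose a 3-point intention-to-treat effect came wholly from the face-to-face care. The complier estimate would then credit adherence with 3 / 0.55 = 5.5 to 3 / 0.30 = 10 points. With d = 4, the planned contrast would show 3 + 1.8 = 4.8 to 3 + 2.8 = 5.8.

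What remains is that the article fixes a one-sided selection, attaches a 5% test to it, and names no safeguard aimed at adherence.

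**Conclusion.** The point holds as a moderate defect in a secondary analysis. That selection occurs follows from the definition of the analysis set and needs no assumption. The amount does: for a residual gap of 4 to 6 points, the spurious difference ranges from negligible in practice at high adherence to as much as 70% of the design difference at the lowest adherence considered, with a test that rejects in about 6 to 27% of trials rather than 5%. The calculation is for no true effect; the same term would be added to any real effect that did not depend on adherence. The documents support neither a fixed direction of bias nor doubt about the primary comparison.

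**What to change.** 1. In the per-protocol analysis, weight the adherent intervention patients so that they resemble the full intervention arm on baseline predictors of adherence, or at least adjust for those predictors in the mixed model. All are already collected: STarT Back risk group (essential, because the threshold depends on it), baseline ODI, pain, age, education, self-efficacy and patient activation.
2. Report the result as exploratory and non-causal, with an interval and without a significance claim. Exempt this analysis from the blanket 5% rule, and limit the intention-to-treat sentence to the analyses to which it applies.
3. Optionally add a complier-average causal effect as a sensitivity analysis, stating that the exclusion restriction is doubtful because face-to-face care and training also differ between arms.

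The cost is some extra analysis work and a somewhat wider interval. No new data are needed, and the sample size does not change. Weighting removes only measured baseline differences, not those from stopping the app during follow-up, so the exploratory label is needed even when weights are used.
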